## Abstract

**Background:**

Fibromyalgia a common idiopathic condition affecting around 1.4% of adults globally. Its signature symptom is chronic widespread pain, with a constellation of somatic and psychological symptoms. Fibromyalgia is associated with significant reductions in quality of life, yet to date there is no biochemical marker for its diagnosis. Previous studies have indicated a strong association with gastrointestinal dysfunction, and more recently, alterations to the gut microbiome. No studies have examined the inter-relationship between fibromyalgia, gastrointestinal dysfunction, and the microbiome. This prospective observational case-controlled study will gather data on gastrointestinal function, dietary intake, fermentation patterns of ingested carbohydrates, and symptoms commonly associated with fibromyalgia. These will be evaluated alongside human gene expression and metatranscriptomic analysis of the oral and faecal microbiome.

**Methods:**

Adult women aged ≥18 years diagnosed with fibromyalgia and/or meeting ACR 2016 criteria, and healthy family or age-matched controls will be recruited from the community. From consenting participants, we will collect detailed survey information and samples of blood, urine, stool, saliva, and breath.

**Discussion:**

This is the first prospective study examining interactions between digestive function, human gene expression, and the gut microbiome together with general, and fibromyalgia-specific, symptoms experienced by New Zealand women. This exploration will allow an in-depth understanding of clinically relevant factors that are associated with fibromyalgia and will guide further research and contribute to improved management of this poorly understood condition.

**Trial Registration:**

The study was approved by the New Zealand Health and Disability Committee (HDEC) (ref: 20/CEN/197) and registered with the Australia and New Zealand Clinical Trials Registry (ANZCTR), registration number ACTRN12620001337965. Written consent will be obtained after providing participants with detailed information about the procedures. Access to data will be restricted to the immediate research team, and all samples and survey data will be deidentified and coded before analysis.

## Background

Fibromyalgia is a common, chronic rheumatological condition of unknown aetiology. Since it was first described in 1592 as muscular rheumatism, its definition has evolved [1], and fibromyalgia is now considered a syndrome of widespread body pain, associated with a constellation of symptoms, such as fatigue, depression, headaches, waking unrefreshed and abdominal pain or cramps [2].

The prevalence of fibromyalgia (also previously known as myofascial pain syndrome, fibrositis and fibromyositis) [1] ranges from 0.2% to 6.6%, with women more commonly afflicted than men [3]. It is associated with substantive decreases in quality of life and significant socioeconomic burden, with high direct and indirect costs [4].

The pathophysiology of fibromyalgia remains elusive, which poses challenges for diagnosis and treatment. While there is no clear inflammatory process, several candidates have been proposed as predisposing or exacerbating factors, including infection, oxidative stress, pre-existing autoimmune conditions, genetics, sleep disorders, nervous system dysfunction, changes in epidermal nerve fibres, and hormonal dysregulation [5]. While none have proven to be universal or predictive of the condition, recent guidelines recommend focusing on immunological markers, specifically auto-immune antibodies [6].

There are currently no laboratory evaluations that aid accurate determination of fibromyalgia. Testing is done to confirm absence of other pathology, leading to a diagnosis based on subjective evaluation of clinical presentation of pain and concomitant symptoms [2]. Management of fibromyalgia typically centres around mitigation of the predominant symptoms (pain, sleep, and mood) with pharmaceutical agents and supportive therapies such as stress management and exercise commonly recommended [7].

Among the range of associated somatic symptoms is a high prevalence of gastrointestinal dysfunction. Functional gastrointestinal disorders (FGIDs), recently redefined as *Disorders of Gut-Brain Interaction (DGBI)* [8], encompass a range of gastrointestinal disorders for which no structural basis can be found. Symptoms are believed to be due to interactions between the gut microbiota, immune function in the gastrointestinal tract, altered sensitivity of the viscera, and dysregulation of the central nervous system. Irritable bowel syndrome (IBS) is the most common of the FGIDs, and is commonly comorbid in people with fibromyalgia, as explored in our systematic review [9]. Additional reports have demonstrated that impaired digestive dysfunction impacts the severity of fibromyalgia symptoms [10, 11]. The FGIDs are increasingly associated with alterations in the composition, diversity, and function of the gastrointestinal microbiota [12], with recent findings of distinctive differences between the gut microbiome in those with fibromyalgia compared to healthy controls [13]. Existing literature exploring relationships associated with the gut microbiota and its biochemical markers were explored in an additional systematic review [14].

The concept of a gut-musculoskeletal axis is a recent one. Several targets for interaction have been proposed, including gut microbial interactions with available nutrients [15], impaired intestinal integrity [16], modulation of immune cell function [17], and translocation of microbial by-products, such as lipopolysaccharides (LPS) from gram-negative organisms. Notably, recent explorations into associations between both composition and function of gut microbiota and fibromyalgia, discovering demonstrable links. Minerbi et al [18] identified gut-microbiota associated serum markers that were able to differentiate between fibromyalgics and controls. Work is ongoing in this area.

Additionally, a gut-microbiome-immune axis has also been proposed [19]. Mechanisms subsequent to impaired intestinal barrier have been described as important predisposing, or possibly instrumental, factors in the development of a range of autoimmune diseases [16, 20]. Microbial LPS is associated with immunosuppression, and an inability to tolerate this endotoxin is a candidate for contribution to development of autoimmunity [21]. A range of additional proposed mechanisms are explored by Li et al [22]. Yet to be confirmed is cause versus effect in these relationships, and whether fibromyalgia is an autoimmune condition or not.

To date, no studies have explored the intersection between the gut (oral and faecal) microbiota, the FGID/DGBI and the complex symptom presentation in people with fibromyalgia. The FIDGIT study explores this intersection and aims to provide insights into these relationships.

## Objectives

The primary aim of this clinical study is to investigate the relationships between the composition and function of the oral and gastrointestinal microbiota, digestive symptoms, and clinical presentation of adult women living with fibromyalgia and compare these to age or family-matched healthy female controls.

The specific aims are to assess and contrast: (A) the interaction between the oral and faecal microbiome, including its function, complexity, and diversity, and (i) digestive symptoms; (ii) symptoms associated with fibromyalgia; (iii) human gene expression, and (B) the interaction between digestive symptoms and symptoms associated with fibromyalgia. We will also examine these factors in relationship to the human transcriptome.

Factors known to influence the composition of the gut microbiome, including oral health, diet, sleep, body composition, medication and supplement use will be evaluated. We will also evaluate redox balance, glycaemic control, and environmental mould exposure.

The study is designed to test the hypothesis that the gut microbiome, and its transcriptome, is associated with digestive function, and the symptoms associated with fibromyalgia.

Here we detail the study protocol, recruitment strategy and analytical procedures.

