#### Inclusion and exclusion criteria

Women aged 18 to 75 years, meeting fibromyalgia criteria as defined by the American College of Rheumatology (2016) (ACR2016), or with a formal diagnosis by a medical practitioner, and willing to comply with study requirements, including travelling to the study site in Auckland, NZ, will be invited to join the study.

Exclusion criteria for both groups include being a current smoker, having a diagnosis of diabetes mellitus, being pregnant or breastfeeding, having any major comorbid illness (e.g., malignancy, active inflammatory or metabolic disease), or being unable to withhold anti-inflammatory medication for at least 48 hours. At least 4 weeks must lapse after any antibiotic treatment before enrolment.

Healthy controls must meet the same criteria, except they must *not* meet criteria for fibromyalgia.

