#### Recruitment

A study website has been designed to enhance the recruitment phase of this study. The site contains information about the project, details on the study design, and a link to the eligibility survey, hosted on REDCap. Links to this website, along with summary information, will be provided to a range of health professionals thought to have interactions with people with fibromyalgia. Printed flyers will be distributed to medical centres, allied health clinics and pharmacies, and displayed on community and library noticeboards within a 5km radius of the study site. As each participant completes submission of study samples, a report detailing the available results will be sent to them and their medical practitioner. A brief outline of the study will be included, along with a recruitment flyer.

In addition, the study will be promoted via advertisements and social media posts via support groups and community pages, including the Facebook page of Fibromyalgia NZ.

Volunteers with fibromyalgia will be requested to invite a healthy adult female who is a family member (sister, daughter, mother), household cohabitant or close friend to participate to form our control group. Where numbers for controls are lacking, age-matched controls will be sought via social and professional networks.

In lieu of financial compensation to volunteers, each participant will receive a report detailing results from tests analysed at the study site. Together these have a retail value of more than NZ$500.

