### Statistical analysis

All data will be anonymised and saved in password protected computer hosted on the University of Sydney’s Data Management System. Statistical analysis will be performed using specialist software. The level of significance will be set at *p* < 0.05.

Descriptive statistics will be used to detail the characteristics of the cohort, and the students’ t-test will be employed to compare participants and controls. Anthropometrics, symptom prevalence, scores and co-morbidities will be compared using univariate and multivariate analysis of variance, as appropriate.

After clustering data according to conventions appropriate to each of the questionnaires in the participant survey, group differences will be assessed using students’ t-tests, Wilcoxon signed-rank test chi-squared tests, and logistic regression, as appropriate.

For microbiome analyses, after stratification by age-groups to allow for variances that may be associated with reproductive life-stages, correction for multiple comparisons (e.g., using Benjamini–Hochberg FDR) and normalised operational taxonomy units will be evaluated using Pearson's correlations. Strength of associations with clinical variables will be tested using Spearman's Rho. Further statistical analysis of the data will be performed using machine learning methods.

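### Controls are labelled age- or family-matched, but the recruitment rule does not secure this, and the clinical and questionnaire comparisons name no age term

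*Protocol article*

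**What the plan says.** **Label.** In the protocol article, the Methods paragraph of the Abstract states that "healthy family or age-matched controls will be recruited from the community". The Objectives set out to "compare these to age or family-matched healthy female controls". Participants and recruitment plans at least 100 cases and a minimum of 50 controls, and describes the controls as matched.

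**Rule.** The Recruitment section asks each volunteer with fibromyalgia to invite "a healthy adult female who is a family member (sister, daughter, mother), household cohabitant or close friend". It attaches no age condition to that invitation. Age matching appears only as a second step: "Where numbers for controls are lacking, age-matched controls will be sought via social and professional networks".

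**Age limits.** Inclusion and exclusion criteria opens with "Women aged 18 to 75 years, meeting fibromyalgia criteria" and holds controls to the same criteria, apart from fibromyalgia status. Controls are therefore also 18 to 75 years old.

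**Analysis.** Statistical analysis says that the t-test "will be employed to compare participants and controls". Anthropometrics, symptoms, scores and co-morbidities go to univariate and multivariate analysis of variance. Questionnaire data go to t-tests, a Wilcoxon signed-rank test, chi-squared tests and logistic regression, as appropriate. Age is mentioned once, as the basis for stratifying the microbiome analyses, and the reason given is variation linked to reproductive life-stage.

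**The concern.** A reader who sees the word matched will assume that the two groups are comparable in age, or at least that each control is related to a case. The recruitment rule guarantees neither. If the nominated women are on balance younger or older than the cases, any measure that changes with age will differ between the groups without any contribution from fibromyalgia. Body composition, sleep, glycaemic control and redox balance are plausible examples, and the Objectives list all four for evaluation. The protocol itself treats age as a source of variation for the microbiome but does not carry that through to the other data. Digestive symptoms and clinical presentation are part of the primary aim, so the affected comparisons are not peripheral.

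**Working it through.** The protocol gives no figure for age balance, so there is none to reproduce. The check has two parts.

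**1. Does each recruitment route deliver what the label promises?**

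| Route (Recruitment section) | Family? | Age-matched by rule? | Fits the label in the Objectives? |
|---|---|---|---|
| Sister | yes | no | yes, as family |
| Mother or daughter | yes | no, usually a generation apart | yes, as family |
| Household cohabitant | not required | no | no |
| Close friend | not required | no | no |
| Fallback control | not required | yes | yes, as age-matched |

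The direct conflict of wording is confined to cohabitants and friends. The lack of assured age balance applies to every route except the fallback. The eligibility limits leave a span of 75 − 18 = 57 years.

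**2. What would an age imbalance do to an unadjusted test?**

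Inputs from the protocol: n1 = 100 cases and n2 = 50 controls (Participants and recruitment); significance level 0.05 (Statistical analysis). The protocol does not say whether tests are one- or two-sided; I take two-sided.

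Inputs that are assumptions: D, the case-control difference in mean age in SDs of age (0.25 to 0.5), and r, the correlation of the outcome with age (0.2 to 0.4). I also assume that the relation with age is linear and the same in both groups, that fibromyalgia has no true effect on the outcome, and that the normal approximation holds.

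- Bias of the group difference, in SDs of the outcome: r × D.
- Standard error of the difference, in the same units: √(1/100 + 1/50) = √0.03 = 0.173.
- Standardised shift: s = r × D / 0.173.
- False-positive rate: Φ(s − 1.96) + Φ(−s − 1.96).

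Low corner, D = 0.25 and r = 0.2: bias 0.05 SD, s = 0.05/0.173 = 0.29, false-positive rate 6.0%.

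High corner, D = 0.5 and r = 0.4: bias 0.20 SD, s = 0.20/0.173 = 1.15, false-positive rate 21.1%.

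| Age gap D | r = 0.2 | r = 0.3 | r = 0.4 |
|---|---|---|---|
| 0 | 5.0% | 5.0% | 5.0% |
| 0.25 SD | 6.0% | 7.2% | 8.9% |
| 0.5 SD | 8.9% | 13.9% | 21.1% |

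The Sample size section names 55 per group instead. At 55 v 55 the standard error is √(2/55) = 0.191, and the same two corners give 5.8% and 18.2%, so the choice of sample size hardly matters here.

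**The case against.** Four replies have weight.

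- **The label says age or family.** A sister, mother or daughter satisfies it, and the Objectives never promise that family controls match on age. This stands. A reader might infer that mothers and daughters contradict the label; they do not. For them the issue is possible confounding, not inconsistency.
- **Age is bounded.** The Recruitment section speaks of an adult female, and a reader might infer that controls may be of any adult age. The eligibility criteria limit them to 18 to 75 years, as for cases. This stands too, although it leaves ample room for imbalance.
- **Adjusted analysis is not excluded.** Logistic regression and multivariate analysis of variance are listed, the choice is left open, and a fuller analysis plan may exist. A reader might infer a commitment to unadjusted analysis throughout; the text does not go that far, and the microbiome analyses are stratified by age group. What remains is that no age term is named for the other comparisons, and that the t-test, which is the named comparison of cases and controls, cannot carry one, nor can the chi-squared test as listed. A later plan could adjust those comparisons only by replacing the published method.
- **The size is hypothetical.** Nothing in the document shows that an imbalance will arise or in which direction. Mothers and daughters may offset each other, and sisters, friends and fallback controls may be close to the cases in age. This stands, and it limits what can be claimed about magnitude. It does not remove the case for adjusting in advance, since the direction cannot be foreseen.

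**Conclusion.** The point holds in a limited form. The protocol describes its controls as matched in three places, but its main recruitment route admits cohabitants and friends who need be neither family nor age-matched, and age matching is only a fallback. Outside the microbiome analyses, the case-control comparisons are set with no age term, so a net age imbalance would pass straight into them. At 100 v 50, assumed gaps of 0.25 to 0.5 SD and correlations of 0.2 to 0.4 give a false-positive rate of about 6% to 21% in place of 5%; with no imbalance there is no bias. These figures illustrate the mechanism and do not predict this study's error rate. The change is worth making because a better analysis is available at almost no cost.

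**What to change.** 1. Describe the controls as nominated by the case (relative, cohabitant or friend), or age-matched where none is nominated. Use the same description in the Abstract, the Objectives, Participants and recruitment, and Recruitment.
2. For the non-microbiome case-control comparisons, specify linear models for continuous outcomes and logistic models for binary ones, with age as a continuous covariate. Keep the t-test and the chi-squared test as descriptive.
3. Optionally, use the fallback recruits to balance the age distribution of the control group as well as to fill numbers.

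Items 1 and 2 cost a change of wording and one covariate, which is already needed to check eligibility and to form the planned age strata. They need no extra participants or procedures. Item 3 needs some monitoring of age during accrual and helps only if it starts before recruitment ends. An age term does not deal with the link between a nominated control and her case; if the pairing is to be used in the analysis, that has to be stated separately.

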## Methods/study design

### Conceptual framework and study design

We will investigate associations between the oral and faecal metatranscriptome, human transcriptome, FGIDs, indices of intestinal carbohydrate fermentation, diet, oxidative stress, and symptoms associated with fibromyalgia.

### Participants and recruitment

This is a prospective, single-centre, cross-sectional case-controlled, observational study. We aim to recruit at least 100 adult women meeting fibromyalgia diagnostic criteria and a minimum of 50 matched controls. Limiting the study to females reduces the confounding influence of gender difference on gastrointestinal function and the gut microbiome. To determine suitability for inclusion as a participant or as a healthy control, initial screening will be conducted via a survey hosted on Research Electronic Data Capture (REDCap) (via the University of Sydney). Prospective volunteers will then be contacted directly by the study co-ordinator to confirm suitability and book appointments as appropriate.

#### Sample size

Based on 2002 data, the estimated prevalence of fibromyalgia in the NZ population (~5 million) is 1.5% [23]. Up to 98% of women with fibromyalgia may have at least one FGID [24], thus for alpha of 0.05 and confidence interval (CI) of 95%, no less than 55 participants and 55 controls are required.

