## Discussion

This observational study will contribute extensive data on the interaction between the gut microbiota, digestive function, oxidative stress, diet, human gene expression and multiple symptoms associated with fibromyalgia in adult women. It will advance understanding of these inter-relationships and contribute to a deeper understanding of the aetiology of fibromyalgia and the role of the gut microbiome and its gene expression in this condition.

The study has the potential to shed light on areas where scientific understanding is currently lacking. It will contribute to a broader comprehension of the pathophysiology underlying fibromyalgia and its link to functional gut disorders. It may also contribute directly or indirectly to possible laboratory markers that can be used in either diagnosis or monitoring of fibromyalgia.

In addition, the findings will guide future intervention studies involving specific approaches, and potentially, microbiota-based therapies to improve outcomes for people living with fibromyalgia globally.

Limitations. Some level of attrition is expected, especially given the commitment required to complete the extensive testing outlined. Ideally, all samples collection should take place over 2-3 weeks; it is anticipated that not all participants will manage this. Any participant who does not complete the comprehensive study survey will be excluded. Any significant deviations from our study plan will be updated on the ANZCTR registry, with notification to HDEC if appropriate.

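### The plan states two different control minimums (55 required, 50 to be recruited), and the 55 cannot be derived from the inputs given for it

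*Protocol article*

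**What the plan says.** Two adjacent sections of the protocol article set a minimum for the control group.

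- Participants and recruitment: "We aim to recruit at least 100 adult women meeting fibromyalgia diagnostic criteria and a minimum of 50 matched controls".
- Sample size: "no less than 55 participants and 55 controls are required".

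The Sample size section presents its figure as a consequence of what precedes it. The inputs are that "the estimated prevalence of fibromyalgia in the NZ population (~5 million) is 1.5"%, that "Up to 98% of women with fibromyalgia may have at least one FGID", and the phrase "thus for alpha of 0.05 and confidence interval (CI) of 95"%. It gives no power, margin of error, control-group rate or target difference.

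The limitations paragraph of the Discussion adds: "Some level of attrition is expected, especially given the commitment required to complete the extensive testing outlined". It also excludes any woman who does not complete the study survey. No attrition rate is given, and neither minimum is said to count recruited or analysed women.

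**The concern.** Both sentences set a floor for the same group, and the floors differ. A team that closes control recruitment at 50 has done what one section asks and missed what the other calls required. A later reader then has no agreed standard for judging whether the study reached its size. The control floor may well be the one that binds, because the Recruitment section already provides for a shortage of controls.

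The second problem is the derivation. The article does more than omit details that a fuller document might hold: it offers a chain of reasoning ending in 55, and that chain does not lead there. Readers are told that 55 per group is statistically required when the stated basis cannot show it. The basis is also away from the main question. The hypothesis under Objectives concerns associations of the microbiome and its transcriptome with digestive function and symptoms, and the frequency of functional gut disorders in cases does not size that.

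**Working it through.** **1. The two floors.** Required controls 55, recruitment minimum 50. Shortfall 55 − 50 = 5, and 5/55 = 9.1%. For cases the recruitment floor (100) exceeds 55, and the total (150) exceeds 110. The conflict concerns controls only.

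**2. Can 55 be reproduced?** Stated inputs: 98% (cases, an upper figure), 1.5% (population), alpha 0.05, which is the same information as 95% confidence. Two-sided testing is assumed. The method is not named, so the two usual routes were tried.

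*Single proportion,* n = 1.96² × p(1 − p)/d²:

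| p | margin d | n |
|---|---|---|
| 0.98 | 0.05 | 30.1 |
| 0.98 | 0.04 | 47.1 |
| 0.98 | 0.037 | 55.0 |
| 0.98 | 0.03 | 83.7 |
| 0.015 | 0.05 | 22.7 |
| 0.015 | 0.032 | 55.4 |
| 0.015 | 0.03 | 63.1 |

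A finite-population correction (for 5 million, or for 1.5% × 5 million = 75,000) changes none of these materially. A margin of 3.7 points at 98%, or about 3.2 points at 1.5%, gives 55. Neither margin is stated.

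*Two proportions, equal groups,* 80% power (assumed), no continuity correction: n = [1.96√(2p̄(1 − p̄)) + 0.842√(p₁(1 − p₁) + p₂(1 − p₂))]²/(p₁ − p₂)², with p₁ = 0.98.

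For p₂ = 0.82: p̄ = 0.90, so n = (1.96 × 0.424 + 0.842 × 0.409)²/0.16² = 1.382/0.0256 = 54 per group.

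| assumed control rate | n per group |
|---|---|
| 50% | 12 |
| 70% | 26 |
| 80% | 47 |
| 82% | 54 |
| 90% | 138 |

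So 55 needs a control rate of about 82% at 80% power. At 90% power it needs about 78%. Neither the rate nor the power is stated. Using 1.5% as the comparator gives 3 to 5 per group.

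The plan's figure is therefore not reproduced from its own inputs, although several unstated assumptions reach it.

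**3. Does the lower control floor cost power?** Detectable standardised difference, two-sample t-test, 80% power, two-sided 0.05, groups treated as independent. Approximately d = (1.96 + 0.842) × √(1/n₁ + 1/n₂); the last column is the exact t-test value.

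| cases:controls | √(1/n₁ + 1/n₂) | detectable d |
|---|---|---|
| 55:55 | 0.191 | 0.539 |
| 100:50 | 0.173 | 0.488 |
| 100:45 | 0.180 | 0.506 |
| 90:45 | 0.183 | 0.515 |
| 55:50 | 0.195 | 0.553 |

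The planned 100:50 is equivalent to 2/(1/50 + 1/100) = 66.7 per group at equal allocation. With 50 controls, matching the precision of 55:55 needs 1/n₁ = 2/55 − 1/50 = 0.01636, that is 62 cases. With 45 controls it needs 1/n₁ = 2/55 − 1/45 = 0.01414, that is 71 cases.

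**The case against.** The strongest reply is that both figures are floors. Recruiting 55 or more controls satisfies both sections, and the Recruitment section names a back-up source of controls. The plan allows a shortfall; it does not build one in. This stands, so a reader who infers that the study must fail its own size goes further than the text.

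A reader might also infer that the study is underpowered because of the mismatch. The figures do not support that: 100:50 is more precise than 55:55, and remains so unless case numbers fall well below target.

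A third tempting reading is that 55 is an arithmetical error, or that it comes from a precision calculation for a single proportion. The document names no method, and its equal groups fit a two-group test as well. The 55 can be reached by more than one route, so it cannot be called wrong. Criticism that rests on one presumed method, such as saying that 98% was chosen to give the smallest sample, would be conjecture.

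Finally, this is a condensed article, and the missing power, margin and control rate may stand in a fuller protocol. Their absence alone would be no finding. What survives is what the article does say: two floors that disagree, and a stated derivation that does not yield its result.

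**Conclusion.** The point holds in two limited parts, and should be fixed.

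- The control minimum is stated as 55 in one section and 50 in the next, a gap of 5 (9%), with attrition expected and no statement of whether recruited or analysed women are counted.
- The figure of 55 does not follow from the inputs offered for it. It is underivable as written, not shown to be numerically wrong.

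The consequence is one of standard and justification rather than lost power. If 100 cases are reached, 100:50 detects 0.49 against 0.54 for 55:55. That comparison assumes 80% power, two-sided 0.05 and independent groups. It makes no allowance for the matching or family links between cases and controls, which the article describes but does not quantify. It concerns a single between-group contrast and says nothing about power for microbiome associations after correction for multiple comparisons.

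**What to change.** 1. Give one control minimum in both Participants and recruitment and Sample size, and say whether it counts recruited or analysed women.
2. Withdraw the claim that 55 and 55 are required on the strength of the 1.5% and 98% figures.
3. State instead what the planned 100:50 delivers at the analysable numbers that the sponsor expects. With 80% power, two-sided 0.05 and groups treated as independent, the detectable standardised difference is about 0.49 with no attrition, 0.51 at 100:45, and 0.51 to 0.52 at 90:45 (normal approximation and exact t-test). The two attrition cases are illustrations, since the article gives no rate.
4. Add that this sizes the between-group contrast and not the multiplicity-corrected microbiome associations.

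The cost is rewording two sections; no extra participants are needed. The price is a less favourable justification, because the text would describe what the chosen numbers can detect and no longer present them as a derived requirement. If the sponsor holds a calculation that yields 55, the alternative is to state its control rate or margin, power and allocation ratio, and raise the recruitment floor to match.
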